### Safety monitoring and adverse events

2.14

Participants will be observed daily for adverse effects. All adverse events will be documented, assessed using WHO–UMC causality assessment, and managed appropriately (16).

### Rescue medications

2.15

In case of rapid aggravation of symptoms, the trial will be stopped, and the participant will be referred to a tertiary health care center for advanced management, including pharmacological strategies.

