### Study design

2.1

This is an open-label, parallel-group, exploratory randomized controlled trial designed to evaluate the efficacy and safety of a therapeutic polyherbal infusion (Kharjuradi Mantha) as an adjunct to multidisciplinary relaxation techniques in the management of mild-to-moderate AWS.

In the present study setting, multidisciplinary relaxation techniques constitute the baseline standard of care in the management of mild-to-moderate AWS in accordance with NAPDDR Guidelines. In moderate cases, these interventions will be continued under strict monitoring with a protocol for escalation to pharmacological management if required. A similar pre-defined pharmacological protocol with benzodiazepines is in place, and patients requiring such management will be excluded at baseline or managed accordingly by adopting the rescue medication strategy. This protocol does not aim to replace standard pharmacotherapy; however, it aims to evaluate the efficacy of the polyherbal infusion as an adjunct to the standard supportive care in patients with mild-to-moderate AWS.

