### Eligibility criteria

2.4

The inclusion criteria for this trial include male participants aged between 25 and 60 years, those who are diagnosed with mild-to-moderate AWS (CIWA-AR score 8–15) (14), those who are willing to participate and provide written informed consent, and residents who are already undergoing non-pharmacological management for alcohol withdrawal. Patients with severe withdrawal (CIWA-AR > 15) or delirium tremens, hepatic failure, ischemic heart disease, or uncontrolled metabolic disorders; those who are currently on psychotropic or hepatotoxic medication; those who are diagnosed with any major psychiatric disorders; or those who are in concurrent participation with another clinical trial will be excluded from the study.

All participants will be strictly monitored and continuously evaluated for the progression of symptoms into a severe stage, where a predefined rescue medication protocol will be adopted for conventional management in such cases.

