### Data collection and management

2.12

All the baseline data collected will be mentioned in the case file and in a case report form (CRF), which is specific for each participant, comprising history, examinations, and assessment scales. CIWA-AR is a 10-step questionnaire with well-documented reliability, reproducibility, validity, and feasibility in clinical settings and has been administered here to assess the symptoms. Trial adherence will be assured by scheduling subsequent visit reminders, and the follow-up data will be mentioned in the case file as well as the CRF. Even if a patient wants to withdraw from the trial or if they are not complying with the treatment, the case file and CRF will be documented for record purposes.

Data entry will be done as a soft copy in secured databases and recorded manually as a hard copy in the CRF. The values will be cross-checked by the co-investigator before uploading into the database, and all the data will be rechecked before submitting for final analysis.

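### The rescue rules differ between sections, and a participant who worsens and is referred out is likely to have no post-baseline CIWA-AR score

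*Protocol article*

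**What the plan says.** All references are to the protocol article.

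- **Section 2.1 (Study design).** For moderate cases, "these interventions will be continued under strict monitoring with a protocol for escalation to pharmacological management if required". On drug treatment, "patients requiring such management will be excluded at baseline or managed accordingly by adopting the rescue medication strategy".
- **Section 2.4 (Eligibility criteria).** If symptoms progress to a severe stage, "a predefined rescue medication protocol will be adopted for conventional management in such cases". Stopping and referral are not mentioned.
- **Section 2.15 (Rescue medications).** "In case of rapid aggravation of symptoms, the trial will be stopped, and the participant will be referred to a tertiary health care center". Drug treatment appears only as part of what the receiving centre may provide.
- **Section 2.8 and Table 5.** CIWA-AR is assessed on Day 0 and Day 29. The second-week visit reviews adverse events and has no CIWA-AR entry.
- **Abstract, Methods.** The final score is taken in the trial setting.
- **Section 2.12.** "Even if a patient wants to withdraw from the trial or if they are not complying with the treatment, the case file and CRF" are kept: "the case file and CRF will be documented for record purposes".
- **Section 2.13.** The tests are paired t-tests, independent t-tests and repeated-measures ANOVA, with p < 0.05 as the criterion.

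**The concern.** There are two linked problems.

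First, the sections on worsening do not line up. Sections 2.1 and 2.4 point to a predefined rescue medication protocol. The section carrying that title describes stopping and referral. The triggers also differ: need for drug treatment (2.1), progression to a severe stage (2.4) and rapid aggravation (2.15). It is also unclear whether the trial that stops is the participant's treatment, the participant's participation or the whole study.

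Second, the schedule makes it likely that a referred participant has only a baseline score. The reason for the missing score is the condition that the score measures. The Introduction gives prevention of progression to severe withdrawal as part of the rationale, so those most informative about that aim are the likeliest to leave the comparison. Investigators are not blinded (Section 2.11) and Section 2.15 gives no threshold for rapid aggravation, so referral could differ by arm.

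**Working it through.** **The plan's own figure.** Section 2.9 gives 38 participants, 19 per arm: 2 × 19 = 38. It states no effect size, SD, power or dropout rate, so there is no power calculation to reproduce. For scale, 19 per arm with a two-sided 5% t-test (sidedness assumed) and 80% power detects a difference of 0.934 SD.

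**Why the tests cannot use such a participant.** Change = Day 29 score − Day 0 score. With no Day 29 score there is no change for the independent t-test and no pair for the paired t-test. With two time points, repeated-measures ANOVA has no second value either.

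**Assumptions for size.** Outcomes are normal with SD 1, 19 per arm, higher is worse, and a negative difference favours the infusion. The number lost and the true effect are not in the document, so ranges are shown. Rejection rates come from 20,000 simulated trials per setting.

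**(a) No true effect, the worst k of 19 lost in one arm only.** The arm's mean falls by (sum of the k largest expected values among 19 standard normal draws) / (19 − k). The four largest are 1.844, 1.380, 1.099 and 0.886.

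- k = 2: (1.844 + 1.380) / 17 = 3.224 / 17 = 0.190 SD. Simulation: 0.19 SD, false-positive rate 10%.
- k = 4: (1.844 + 1.380 + 1.099 + 0.886) / 15 = 5.209 / 15 = 0.347 SD. Simulation: 0.35 SD, false-positive rate 20%.

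The sign follows the arm with the losses: −0.19 and −0.35 if it is the infusion arm, +0.19 and +0.35 if it is the control arm. Against the detectable difference these are 0.190 / 0.934 = 20% and 0.347 / 0.934 = 37%.

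**(b) True difference −0.8 SD, the same worsening threshold c in both arms.** Mean of those retained: control −φ(c)/Φ(c); infusion −0.8 − φ(c + 0.8)/Φ(c + 0.8).

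| c | Lost, control | Lost, infusion | Retained means (infusion, control) | Difference | Simulated power |
|---|---|---|---|---|---|
| 1.5 | 7% | 1% | −0.829, −0.139 | −0.69 | 59% |
| 1.0 | 16% | 4% | −0.882, −0.288 | −0.59 | 49% |
| 0.5 | 31% | 10% | −0.990, −0.509 | −0.48 | 36% |

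With nobody lost, simulated power is about 67%. A real benefit is understated because the arm with less benefit loses more of its worst cases.

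**(c) No true effect, the same threshold in both arms.** The simulated difference is 0 to within 0.003 and the rejection rate is about 5%. If instead a fixed equal number of worst cases (1, 2 or 4) is lost from each arm, the estimate is still unbiased. The rejection rate is then 7%, 8% or 10%, because cutting off the tails makes the SD too small.

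**The case against.** **The analysis rules may sit elsewhere.** Analysis sets, missing data and handling of rescue are commonly left to a full protocol or analysis plan, and neither is shown. This stands for the analysis rules, whose absence from an article is no defect. It does not stand for data collection: the schedule and the stop-and-refer rule are stated here, and an analysis plan cannot restore a score that nobody took.

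**The sections can be read together.** Section 2.15 may simply be the rescue strategy that 2.1 and 2.4 mention, and its singular reference to the participant makes a whole-study stop an unlikely meaning. That is fair, and it makes part of the fix a matter of wording. The differing triggers and the lack of a medication protocol under that heading remain.

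**Worsening is not hidden from safety reporting.** Section 2.4 provides continuous evaluation, Section 2.14 daily observation and documentation of adverse events, and Section 3 notification to the ethics committee. This stands. The concern is the efficacy comparison.

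Four stronger readings are tempting but not supported:

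- *Forms of those who worsen are kept for the record and left out of the analysis.* The sentence in 2.12 concerns withdrawal and non-compliance, does not mention worsening, and does not say the data are excluded.
- *The sections contradict each other on whether the participant stays in the trial.* They differ on how rescue is handled. None addresses continued follow-up.
- *The plan deletes the worst outcomes.* No section says so, and 2.8 says both groups are reassessed. Loss is a likely consequence of the schedule and the referral, not a stated rule.
- *The bias is larger than the trial can detect.* Suppose 16 of 19 average 3 points and three escalate at 18. Then (16 × 3 + 3 × 18) / 19 = 5.37, a shift of 2.37, which exceeds 0.934 × 2 = 1.9 if the SD is 2. But all these inputs are invented, and the shift is in one arm's mean. The SD also does not fit: √{[16 × (2² + 2.37²) + 3 × 12.63²] / 19} ≈ 5.8, for which the detectable difference is 0.934 × 5.8 ≈ 5.4.

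**Conclusion.** The point holds in this form: the rescue provisions in Sections 2.1, 2.4 and 2.15 need reconciling, and under the schedule as written a participant who is stopped and referred is likely to contribute nothing to the only stated efficacy outcome. The loss depends on the outcome, but its direction is not fixed. A one-sided loss of the worst 2 to 4 of 19 moves the estimate by about 0.19 to 0.35 SD towards that arm and raises the false-positive rate to about 10 to 20%. Equal rules with a true effect of 0.8 SD shrink it to between 0.69 and 0.48 SD. Equal losses with no effect give no bias. These sizes rest on normal outcomes and an assumed number lost; the document gives no expected escalation rate. The exploratory aim lowers the stakes, but with 19 per arm a few losses matter and cannot be made good after participants have left.

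**What to change.** 1. Reconcile Sections 2.1, 2.4 and 2.15 on how worsening is handled and what triggers it, and state whether the trial that stops is the participant's treatment, their participation or the study. Which clinical rule applies is for the investigators.
2. State that stopping treatment does not end follow-up, and seek the Day 29 CIWA-AR for every randomised participant, including those referred elsewhere.
3. Document any CIWA-AR available at escalation.
4. Analyse all 38 as randomised and report the number escalated per arm.
5. Add a sensitivity analysis that counts escalation as an unfavourable outcome. Making the escalation score or a worst rank the primary Day 29 value would answer a different question from the observed Day 29 score, so it should not be adopted by default.
6. Clarify in Section 2.12 that data from participants who withdraw or do not comply are included in the analysis.

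Cost: changes of wording, tracing a few referred participants, and possibly a less favourable result.

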## Ethical considerations

3

This study protocol approval has been granted from the Institutional Ethics Committee of Tapovana Ayurvedic Medical College and Hospital, Doddabathi, Davanagere (Approval No. TAMC&H/IEC/01/2024–25, dated 16 July 2024). The trial is prospectively registered with the Clinical Trial Registry of India (CTRI/2024/07/070952).

The study will adhere to the Good Clinical Practice (GCP) guidelines according the Indian Council of Medical Research (ICMR), the Declaration of Helsinki (2013 revision), and the National Ethical Guidelines for Biomedical and Health Research on Human Participants (2017) by ICMR. Patient information leaflets with a comprehensive outlining of the objectives and outcomes of the research will be provided in two languages (English/Kannada). Voluntary written informed consent will be obtained from all participants. Confidentiality of the participant information will be maintained throughout the trial, and data will be securely stored in password-protected databases. Patient enrollment number will be used as part of the identification of the patient during data upload and analysis. Only the Principal Investigator and co-investigator will have access to research data. Safety of the intervention will be prioritized by monitoring and recording any of the adverse events that occur during the trial, followed by notification to the Institute Ethical Committee (IEC). Findings will be published through peer-reviewed journals, conferences, and institutional reports by considering all the scientific, ethical, and safety aspects of the trial.

### Ancillary and post-trial care

3.1

There have been no ancillary studies proposed in the present clinical study. Participants will continue to be provided with the routine standard of care, which is followed in the study setting.

## Discussion

4

This exploratory randomized study aims to evaluate the efficacy of a therapeutic herbal infusion (Kharjuradi Mantha) as an adjunct to yoga, meditation, and counseling in the management of AWS. With rising incidents of clinical challenges and escalation into severe complications, there is an increasing interest in alternative approaches, which include the integration of herbal remedial measures with multidisciplinary relaxation techniques in the uncomplicated stages of AWS. Establishing a pharmacological basis backed with safe and effective findings may contribute to the growing literature that supports an integrative management framework in this condition.

Ayurveda firmly establishes the principle of “countering with the opposite” where the properties of ingredients in a medicine or preparation could act against the doshas (morbid factors) of a disease (17). A majority of the ingredients of the polyherbal infusion “Kharjuradi Mantha” comprise Guru (heavy), Sheeta (cold), and Snigdha (unctuous) Gunas (qualities), which could combat the impact of Laghu (light) Ushna (hot), and Tikshna (sharp) gunas of Madya (alcohol) in AWS. Hence, this would enhance the metabolism and nourishment through Agnidipana and Tarpana gunas of the ingredients, along with the regulation of the movement of Vata as well as Pitta dosha. The majority of the ingredients of Kharjuradi Mantha have vatapitta shamaka properties and are predominant with madhura-amla rasa, which is beneficial in combatting the properties of Madya (18, 19). Other concomitant relaxation techniques would be concentrating on the satva and optimizing the manodoshas (Rajas and Tamas), thereby encompassing the psychological aspects of Madatyaya (20).

Alcohol induces long-term detrimental changes in neurons after repeated detoxification (which is the “kindling phenomenon”), along with brain hyperexcitability caused by abrupt alcohol cessation that upregulates the NMDA receptors (21). Individual pharmacological activities exerted by the bioactive principles of each ingredient collectively constitute the reduction in the symptoms of AWS as well as alcohol-induced systemic toxicities. Various phytopharmacological reviews of the main ingredient Kharjura (*Phoenix dactylifera*) demonstrate anti-inflammatory and antioxidant activity by free radical scavenging action and hepatoprotective activity by effectively reducing the hepatic markers, thereby contributing to potential regulation in AWS (22). Moreover, all the other ingredients also possess the same pharmacological activities, whereas Dadima (Punica grantum) and Amalaki (*Emblica officinalis*) possess an additional neuroprotective action, which could rectify the pathophysiological framework of AWS (23, 24). Several preclinical studies suggest that resveratrol, which is a common constituent in Draksha (*Vitis vinifera*), enhances GABAergic inhibition, possesses anxiolytic activities, and downregulates glutamate-induced cytotoxicity, which leads to hyperexcitation in AWS (25). The major ingredient Kharjura (*Phoenix dactylifera*) and polyphenols in other ingredients like Dadima ameliorate glutamate-induced excitotoxicity, which could be highly contributing to the rectification (26).

Umhau et al. studied the cerebrospinal fluid levels of monocyte chemoattractant protein-1 (MCP-1), as well as interleukin-1β along with tumor necrosis factor-*α* in 28 alcoholics and 13 healthy volunteers, and reported higher levels of MCP-1 in alcoholics, which were positively associated with peripheral markers of alcohol-induced liver inflammation, i.e., serum gamma-glutamyl transferase and aspartate aminotransferase levels in alcoholics. This finding necessarily indicates the elevated inflammatory marker, MCP-1, in accordance with the neurodegeneration and neuroinflammation induced by alcohol (27). Analytical studies of all the ingredients have suggested anti-inflammatory activities of the phytoconstituents in almost all ingredients, which would potentially make it an ideal therapeutic alternative in the management of AWS (23, 28–30).

Concurrently, yoga and meditation promote autonomic balance and psychological stability, while counseling supports behavioral modification30. Moreover, relaxation techniques such as yoga have been found to improve the body’s ability to manage stress, combat inflammatory cytokines, and promote a sense of well-being, which could combat the effects of kindling in AWS (31, 32). Hence, this integrated approach seeks to enhance recovery outcomes, reduce withdrawal severity, and provide a non-dependence-forming alternative to conventional pharmacotherapy. This trial focuses on exploring the efficacy of an augmented approach when a polyherbal infusion of multifaceted action is coupled with the pre-established potency of various relaxing techniques for AWS.

Nevertheless, this trial design has some constraints with respect to its applicability in a larger population. Being an exploratory randomized trial, our primary aim is to generate preliminary-level evidence for further larger trials with multiple arms in a much larger population. The sample size of the study is 38, which would not meet the required criteria for external validity. As it is a time-bound and exploratory study design, non-probability sampling measures were employed, and hence, a small sample size was adopted in this study. Moreover, as there is an academic time limit, assessing the long-term sustained efficacy would not be possible, which could only be carried out by a large sample-sized clinical trial in a prospective cohort setup. Participant and investigator blinding is not feasible, as the appearance and taste could vary while preparing the trial infusion. This study is essentially concentrated on the physical and psychological withdrawal effects in mild and moderate AWS rather than alcohol-related multiple systemic effects, including hepatoprotective effects. Including the assessment of these effects would require much more sophisticated methodologies, and it is beyond the scope of this study.

## Conclusion

5

The outcomes of this trial are expected to deliver sound background clinical evidence regarding the therapeutic efficacy of a polyherbal infusion integrated with multidisciplinary relaxation techniques in improving the subjective presentations and signs in participants with AWS. Anticipated findings could be used as a reference tool for providing a scientific platform for more sophisticated trials incorporating neurochemical and psychometric parameters and thereby exploring the scope of Ayurveda in implementing therapeutic protocols and evidence-based rehabilitation of AWS.
